**Methods:**

This study is a cluster randomised controlled trial at 16 HIV care clinics. A motivational interviewing and cognitive behavioural therapy based intervention for AUDs, developed through adaptation and piloted in Zimbabwe, will be administered to PLWHA with AUDs recruited at HIV clinics. The intervention will be administered over 16 sessions at 8 HIV clinics. This intervention will be compared with an equal attention control in the form of the World Health Organization Mental Health Gap Action Programme (WHO mhGAP) guide, adapted for the Zimbabwean context. General function, quality of life, and adherence to highly active antiretroviral treatment (HAART) will be secondary outcomes. Booster sessions will be administered to both groups at 3 and 6 months respectively.

The primary outcome measure will be the Alcohol Use Disorder Identification Test (AUDIT) score. The World Health Organisation Disability Assessment Schedule 2.0 (WHODAS 2.0), World Health Organisation Quality of Life (WHOQoL) HIV, viral load, and CD4 counts will be secondary outcome measures. Outcome assessments will be administered at baseline, 3, 6, and 12 months. Moderating factors such as perceived social support, how people cope with difficult situations and post-traumatic exposure and experience will be assessed at baseline. Trained research assistants will recruit participants. The outcome assessors who will be trained in administering the outcome and moderating tools will be blinded to the treatment arms allocated to the participants. However, the principal investigator, participants and intervention staff will be unblinded.

Data will be analysed using STATA Version 14. Primary and secondary outcomes will be measured at four time points that is; at baseline, 3, 6, and 12 months respectively. All participants will be included in the analysis of primary and secondary outcome measures. The mean AUDIT scores will be compared between groups using student t-tests. Multilevel logistic regression analysis will be performed for binominal variables and multilevel linear regression for continuous variables. Descriptive statistics will be computed for baseline and follow-up assessments.

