### Design

Two-arm cluster randomised controlled trial at 16 HIV clinics in Zimbabwe, with the unit of randomization HIV clinics, comparing Motivational Enhancement Therapy and Cognitive Behavioural Therapy from Project MATCH adaptation based treatment, with the WHO mhGAP intervention guide, adapted for the local context. This design has been selected to increase administrative efficiency and decrease the risk of experimental contamination at clinic level. The registered general nurses (RGNs) will be trained to administer the intervention and control using manuals.

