### Statistical analysis

#### Sample size

A meta-analysis suggested that a clinically significant difference in negative status on the AUDIT between brief intervention and control of 13% [59]. Shersten et al. [60] describe intra-cluster correlation coefficient in human subjects to be between 0.01 and 0.02 and assumed the intra-cluster correlation in this study to be 0.02. A total of 16 clusters (8 clusters per group) to achieve 80% power to detect a mean difference of 2.5 (with precision of ± 0.45) between the treatment condition means when the standard deviation within a cluster is 4 and the intra-cluster correlation are 0.02 and a significance level of 0.05.

An estimated sample size of 180 patients (90 in the intervention group and 90 in the control group) will be required to detect a difference of 13% between intervention and control groups taking into account the design effect of 1.56. Assuming an attrition rate of 30% (as identified in the pilot study), a total sample size of 240 will be required. Fifteen participants will be randomly selected (with equal probability) at each clinic from a patient number list.

Analysis of covariance (ANCOVAs) and mixed effects linear regression models will be performed for all continuous variables. Generalised linear mixed effects logistic regression model will be performed for binary outcomes. All analyses will allow for within-clinic clustering.

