### Analysis approach

Data will be analysed using STATA Version14 [59]. Primary and secondary outcomes will be measured at four time points: baseline, 3, 6, and 12 months. To account for the stratified cluster trial design, the repeated binary and linear nature of the primary and secondary outcomes, as well as missing data at follow-up, a Generalized Estimation Equations (GEE) approach will be used. Descriptive statistics will be computed for baseline and follow-up assessments. The mean AUDIT scores will be compared using student t-tests. Multilevel logistic regression will be performed for binominal and multilevel linear regression for continuous variables.

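### The Student t-test named for mean AUDIT, read at participant level, conflicts with the protocol's own clustering rule, and no analysis is named as deciding the primary comparison

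*Protocol article*

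**What the plan says.** The Design section describes a two-arm trial "with the unit of randomization HIV clinics". The Sample size section sets 16 clinics, 8 per arm. The Outcome measures section makes the AUDIT score the primary outcome, and Primary outcome tools expresses it as change from baseline.

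Methods that apply to AUDIT appear in three places:

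- **Abstract, Methods:** "The mean AUDIT scores will be compared between groups using student t-tests", followed by multilevel linear regression for continuous variables.
- **Sample size:** ANCOVA and mixed effects linear regression for all continuous variables, and then the general rule "All analyses will allow for within-clinic clustering".
- **Analysis approach:** GEE for the primary and secondary outcomes, chosen to deal with the cluster design, repeated measures and missing follow-up. Descriptive statistics come next, then "The mean AUDIT scores will be compared using student t-tests", then multilevel linear regression for continuous variables.

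The t-test is the only method attached to AUDIT by name. Neither sentence that names it gives its unit (patient or clinic) or its status (primary, supportive or descriptive). No method is called primary anywhere.

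**The concern.** A t-test that compares mean scores between two groups is normally run on individual participants. Here that would treat up to 240 patients as independent when only 16 units were randomised. Patients of one clinic share staff, setting and, in this trial, the nurses who deliver the treatment, so a positive intra-cluster correlation is expected and the protocol itself assumes one. The standard error would then be too small and the p-value too low.

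The second problem is the lack of an order among the methods. With a t-test, ANCOVA, a mixed or multilevel model and GEE all available for one outcome, a significant t-test could stand beside a non-significant clustered model. The protocol has no rule for which is the trial's answer.

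**Working it through.** **Inputs from the protocol (Sample size section).** There are 16 clinics, 8 per arm, with 15 patients per clinic (16 × 15 = 240). The requirement before attrition is 180, or 180/16 = 11.25 per clinic. Attrition is 30%, which leaves 15 × 0.7 = 10.5 per clinic. The cited range is "intra-cluster correlation coefficient in human subjects to be between 0.01 and 0.02", with 0.02 adopted. The stated design effect is 1.56, and the test is at "a significance level of 0.05". Sidedness is not stated, so I assume two-sided.

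**Step 1: the protocol's own design effect.** DE = 1 + (m − 1) × ICC. With m = 15 and ICC = 0.02, DE = 1 + 14 × 0.02 = 1.28, not 1.56. To reach 1.56 takes ICC = 0.56/14 = 0.04 at 15 per clinic, or m = 1 + 0.56/0.02 = 29 per clinic at ICC 0.02. Neither value is in the protocol, so 1.56 cannot be treated as the consequence of its stated inputs.

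**Step 2: type I error of a t-test that ignores clinics.** The true standard error is √DE times the one the test uses. The rejection rate under no effect is therefore approximately 2 × [1 − Φ(1.96/√DE)]. I checked this by simulation with 16 equal clinics, normal data and 100,000 replicates per setting.

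| ICC | Patients per clinic | DE | √DE | Type I error | Simulated |
|---|---|---|---|---|---|
| 0.01 | 11.25 | 1.1025 | 1.050 | 6.2% | 6.2% (11 per clinic) |
| 0.01 | 15 | 1.14 | 1.068 | 6.6% | 6.7% |
| 0.02 | 10.5 | 1.19 | 1.091 | 7.2% | not run |
| 0.02 | 11.25 | 1.205 | 1.098 | 7.4% | 7.4% (11 per clinic) |
| 0.02 | 15 | 1.28 | 1.131 | 8.3% | 8.1% |
| stated DE | – | 1.56 | 1.249 | 11.7% | 11.7% (ICC 0.04, 15 per clinic) |

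For example, at DE 1.28: 1.96/1.131 = 1.732, and 2 × [1 − Φ(1.732)] = 8.3%.

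**Step 3: the same test on clinic means.** In the same simulations, a t-test on the 16 clinic means (16 − 2 = 14 df) rejected in 4.9–5.0% of replicates. The t-test can therefore be valid in this design, but only at clinic level.

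**Step 4: does a valid analysis cost the planned power?** The protocol states: "A total of 16 clusters (8 clusters per group) to achieve 80% power to detect a mean difference of 2.5". With SD 4 and ICC 0.02, the clinic-means t-test on 14 df has about 94% power at 11.25 per clinic and 98% at 15. On the protocol's inputs for the mean difference, an analysis that respects clustering stays well above the 80% target.

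**The case against.** The strongest reply is that the protocol already provides for clustering. The Analysis approach section assigns GEE expressly to the primary and secondary outcomes because of the cluster design. It then adds multilevel linear regression, and the Sample size section applies its clustering rule to every analysis. Read under that rule, the t-test could be one on clinic means. It follows the sentence on descriptive statistics, so it could equally be a simple comparison placed beside the models.

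Much of this stands. A reader might infer that the primary analysis is an individual-level t-test and that the trial's type I error is therefore 7–12%. The text does not support that. Participant level is the ordinary reading but is not written, nothing gives the t-test deciding status, and the 12% end rests on a design effect that the protocol's ICC and clinic size do not produce.

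Nor do the documents establish that the t-test ignores baseline, since the primary outcome is expressed as change from baseline. They do not establish that patients without follow-up are lost from the primary analysis either. GEE is named partly for missing data, and the Participant level section includes everyone.

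The reply does not remove the contradiction. Clinic means are mentioned nowhere, the abstract repeats the t-test without the clustering rule, and listing valid models beside it does not say which result counts.

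**Conclusion.** The plan is wrong as written on a narrower point than an inflated trial-wide error rate. The t-test sentence, on its ordinary reading, conflicts with the protocol's clustering rule, and no single analysis of AUDIT is designated primary.

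The size is conditional. If an unadjusted participant-level t-test were used for inference, the nominal 5% would become 7.2% (10.5 per clinic after attrition) to 8.3% (15 per clinic) at ICC 0.02, and about 6–7% at ICC 0.01. The figure of 11.7% needs a design effect of 1.56. These values assume two-sided testing, equal clinic sizes and approximately normal data. If GEE or the multilevel model is the deciding analysis, the inflation calculated here does not arise. The protocol should say so.

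**What to change.** 1. Delete the t-test sentence in the abstract and in the Analysis approach section. Alternatively, state there that the test is done on the 16 clinic-level means with 14 degrees of freedom.
2. Name one of the cluster-adjusted analyses already listed as the single primary analysis of AUDIT: either GEE or the mixed/multilevel linear model, adjusted for baseline AUDIT and with a small-sample correction for 16 clusters. Describe the other methods as supportive. Either model would meet the point, and its detailed terms can be left to the statistical analysis plan.

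The cost is wording only, with no extra patients, visits or data. Confidence intervals will be slightly wider than those of the unadjusted t-test: by the √DE values above, about 9–13% at ICC 0.02 with 10.5 to 15 per clinic, plus a small allowance for 14 degrees of freedom and before any gain from baseline adjustment.

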#### Ethics

In order to promote quality control and quality assurance of the study, research staff and the principal investigator will receive training in research ethics and good clinical practise. A data research coordinator will ensure accurate data collection and the secure transfer and storage of electronic data. Weekly feedback meetings will be held with study personnel, the data manager, and the project coordinator to address problems and study-related queries.

#### Confidentiality

Participants will be assured of the confidential nature of the study. Anonymity will be maintained by de-identifying collected data and participants will be identifiable by unique identifier codes. Patient-level data will be stored securely on a computer encrypted and password protected for the study team. Files will be stored in a locked cabinet at the University of Zimbabwe College of Health Sciences, Department of Psychiatry for five years.

#### Risks and discomfort

Although no adverse effects are anticipated, participants who experience discomfort or who wish to withdraw for any other reason will be free to do so. Participants who become distressed and uncomfortable with answering the assessment questions which address sensitive topics such as alcohol use and non-adherence and when providing blood samples for CD4 counts and viral loads will be referred to a psychiatrist for further care. Participants will be free to leave the study at any point without prejudice.

#### Interim analysis

Interim statistical analysis will be carried out at 3 and 6 months. A Data and Safety Monitoring Board (DSMB) comprising of experts in HIV/AUDS, an independent statistician and a bioethicist, and the MRCZ will review study-related concerns (e.g. adverse events) that arise. They will review study protocols and procedures (e.g. data collection and storage), as they deem necessary during the data collection phase. Safeguards will be implemented throughout the project to protect participant confidentiality, as described and required by the monitoring board, and to minimize the risk of potential physical and psychological harms.

#### Costs and compensation

Participants will be reimbursed for transport costs and refreshments (US$3) for each visit.

#### Benefits

Participants may directly benefit from the interventions. Any individual identified as alcohol dependent will be referred for alcohol treatment services. Individuals assigned to the MI/CBT intervention may reduce their alcohol consumption, in turn improving HAART adherence and HIV disease outcomes. Clinic staff will benefit as they will be trained in delivering the intervention aimed at reducing harmful/hazardous alcohol consumption. Finally, substantial public health knowledge will likely be gained from this search.

## Discussion

In this study it is hypothesized that an adapted MI/CBT intervention will lead to a significant reduction in alcohol use in PLWHA. It is further hypothesized that reduction in alcohol use will lead to improved function as measured by the WHODAS 2.0, improved quality of life as measured by the WHOQoL HIV, and improved adherence to HAART as measured by the CD4 and viral load. This study further seeks to establish whether registered general nurses in primary health care facilities in Zimbabwe will be effective in providing the MI/CBT intervention to reduce alcohol use and improve patient engagement with treatment.

We will test the effectiveness of an MI/CBT intervention that can be used by RGNs for alcohol reduction in PLWHA. If successful, the intervention will be implemented in HIV clinics in Zimbabwe and other settings where general nurses oversee HIV treatment. We hypothesize that patients may view their ability to return to work as important and this may motivate them to adhere to the treatment. Improved quality of life has been shown to improve adherence in other studies.

Given that most behavioural interventions for alcohol use have been developed within a Western framework, the use of an adapted intervention in this study will inform us about its effectiveness in reducing alcohol use in PLWHA in a resource limited setting. In resource rich environments, inpatient and outpatient services for addictions are usually widely available. However, in Zimbabwe, as in many other resource-limited settings, inpatient management of AUDs may be unaffordable for the majority. Outpatient care, if available, is the rule rather than the exception.

To the authors’ knowledge, no published study from Zimbabwe has examined functioning and quality of life in PLWHA with AUDs. Improvement in functioning and quality of life are key aspects to address in this population. Quality of life has been shown to improve upon initiation of HAART (http://www.stata.com) and studies in other countries have documented an improvement in adherence with an improvement in quality of life [61]. Over a quarter of 15–49 year olds in sub-Saharan Africa are living with AIDS [62]. Given that this is the most productive age group in the community, improving functioning will likely have positive socio-economic impacts on the community.

There are few limitations that warrant mention. Firstly, we will use a self-report screening measure of drinking. Self-report may not accurately reveal drinking quantity and behaviour. That said, the AUDIT has excellent sensitivity and specificity and cross-cultural applicability and can be used in remote areas where sampling for alcohol biomarkers may be challenging. Secondly, brief interventions have been shown to be more useful when provided at community level although the lack training often hampers provision at community level. Thirdly, viral suppression may not correlate well with adherence; even in resource rich settings viral suppression can be low despite an adherence of 80–95%. In this study viral load will be a proxy measure of adherence. CD4 count in addition to the viral load will be used as a measure of adherence.

This is a task-sharing intervention study. It is hoped that, upon successful completion of this study, RGNs from district hospitals and municipal health facilities will be trained in recognising and managing AUDs in HIV infected patients.

## Abbreviations

AIDS: Acquired immunodeficiency syndrome
ANCOVA: Analysis of covariance
AUDIT: Alcohol use disorder identification test
CBT: Cognitive behavioural therapy
CIFG: Comprehensive Intervention fidelity guide
DSMB: Data monitoring and safety board
DTS: Davidson trauma scale
DUDIT: Drug use disorders identification test
FGD: Focus Group Discussion
GEE: Generalized estimation equations
HAART: Highly active antiretroviral therapy
HIV: Human immunodeficiency virus
IHDS: International HIV dementia scale
M.I.N.I.: Mini International neuropsychiatric interview
mhGAP: Mental health gap action programme
MI/CBT: Motivational interviewing/cognitive behavioural therapy
MSPSS: Multidimensional scale of perceived social support
PLWHA: People living with HIV/AIDS
PTSD: Post-traumatic stress disorder
RCT: Randomised controlled trial
RGN: Registered general nurses
SAMISS: Substance abuse mental illness symptom screener
WHO: World Health Organisation
WHODAS: World Health Organisation Disability Assessment Schedule
WHOQoL: World Health Organisation Quality of Life
